#### To examine the effect of the intervention

Analysis of Covariance (ANCOVA) will be performed to examine differences in condom use intentions (at time two and at follow-up), and behaviour. This will control for demographic variables (gender, ethnicity, age), behaviour at time one, and measures of risk appraisal, and coping appraisal.

If the lesson is effective in increasing condom use intentions, mediation analysis [28] will be conducted to identify whether changes in risk appraisals and/or coping appraisals are responsible for this change. This will help to identify the mechanism of change and indicate where future research and/or resources should be focussed.

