The proposed study will use a conditional measure of risk. Given that a large proportion of the sample are not likely to be sexually experienced, participants appraisals of the risk of getting chlamydia if condoms aren’t used will be measured, rather than choosing the alternative ‘if continue with current behaviour’ option. In addition, this will be framed within the context of casual sexual partners for whom STI status is unknown given that this presents the most risky scenario. A further conditional stipulation will be vaginal sex, rather than oral or anal sex. The proposed study will also use an experimental design with follow-up for two months. Examining the motivational hypothesis in the context of an experimental study is ideal since delivery of the intervention should act to ‘destabilise’ existing chlamydia risk appraisals and reduce the predictive relationship between past and future behaviour for those who are already sexually experienced [16].

Whilst an experimental design affords the best circumstances for observing the motivational hypothesis, increasing chlamydia risk appraisals may not be sufficient to motivate condom use. Chlamydia is a single consequence of unprotected sex and evidence suggests that other outcomes of unprotected sex, such as the risk of pregnancy or making sexual experiences more enjoyable, may exert a more powerful effect on condom use intentions [20]. Other authors [13] have also drawn attention to the dyadic context of condom use decision making and the possibility that risk appraisals are not powerful enough to overcome other determinants of behaviour such as embarrassment discussing condom use or uncooperative partners. The proposed study will include a measure of condom use intention as well as behaviour. This is necessary because it is anticipated that a large proportion of the sample will be sexually inexperienced requiring the use of intention as the outcome measure in examining the motivational hypothesis. In addition, it will also enable examination of whether an increase in chlamydia risk appraisals is sufficient to increase condom use intentions and/or behaviour. This will enable conclusions to be drawn about whether a failure to change behaviour is the result of a failure to increase condom use intentions or to overcome the effect of stronger factors operating when intention is translated into behaviour.

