## Methods/design

A two-arm cluster randomised controlled trial (RCT) using a waiting-list control will be used to test the efficacy of an intervention to increase young adults’ intentions to use condoms and actual use of condoms with casual sexual partners compared to a control group (see Figure 1). Secondary school pupils will be invited to participate. The intervention is a single lesson on chlamydia which aims to increase young adults’ chlamydia risk and coping appraisals. We hypothesise that there will be an increase in condom use intentions following delivery of the chlamydia lesson. At the two month follow-up, we hypothesise that there will be a higher rate of condom use during vaginal sex with casual sexual partners amongst sexually experienced participants in the intervention group compared with the control group. At two months, we will also measure condom use intentions to see whether any increases have been maintained over time. We hypothesise any effects of the intervention on condom use intentions or behaviour will be mediated by risk appraisals and/or coping appraisals.

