Pupils will not be obliged to take part. Quizzes will be administered at the same time as questionnaires at all data collection time points to occupy pupils who do not wish to participate. Pupils will not be required to provide their name (participant responses at each time point will be linked through the demographic information supplied). Pupils will be seated in a manner that prevents classmates from overseeing their responses i.e. in exam conditions. All materials (questionnaires and quizzes) will be placed in a sealed envelope by the individual participants and posted into sealed boxes on completion. Teaching staff will not have access to these. Although parental consent will not be required, as parents of participating pupils will have already consented for their children to participate in SRE and related evaluation activities, a letter outlining the study and their child’s involvement will be sent to all parents through each school as a matter of courtesy. Parents will be given the opportunity to ‘opt-out’ their child at this point.

Baseline measures will be: Demographic information (age, date of birth, gender, and ethnicity), perceived likelihood, perceived severity, response efficacy, self-efficacy, past behaviour, and intention to use condoms during vaginal sex with casual sexual partners for whom STI status is unknown. Provisional measures to be taken at baseline, post-intervention and follow-up are provided in Additional file 1.

After the collection of baseline data, schools will be randomised to receive either the school’s usual teaching on STIs and the chlamydia lesson (intervention arm) or the school’s usual teaching on STIs alone (control arm). This enables the study to evaluate the effectiveness of the chlamydia lesson over and above usual practice. As described above, pupils will be blinded to intervention condition. It is not possible to blind teachers to intervention condition but they will be made aware of the importance of delivering teaching that is consistent with their usual practice. Researchers liaising with schools will offer the same guidance and level of support regardless of intervention condition.

As with all trials of this type, there is the potential for drop-out of whole schools during the study. We have no way of estimating the level of this. Drop-out due to unforeseen circumstances will be planned for and a reserve list of schools will be created to expedite the process of additional recruitment if required.

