### Measures post delivery and at follow-up

Immediately following the lessons, a further set of measures will be taken (see Additional file 1). These will be a repeat of those taken at baseline. For those in the intervention arm, a few additional items will be included to allow for process evaluation. These items will measure participants’ enjoyment of the lesson, collect their opinions on the suitability and relevance of the content for their age, and ascertain the extent to which they felt they could relate to the characters and examples given. It will also determine whether participants felt the materials were engaging, and whether the delivery was sufficiently interactive. Items will be a mixture of fixed response and open-ended formats and will allow any necessary improvements to be made to the lesson following evaluation.

At follow-up, three months post delivery, measures of intention and use of condoms (during vaginal sex with casual sexual partners for whom STI status is unknown) will be taken (see Additional file 1).

A number of the lesson exercises are available as ‘games’ on the HPAs e-Bug website. For this reason, it will be necessary to ensure that those in the intervention group have not viewed these prior to delivery of the lesson, and that those in the control group have not viewed these both before or during the study period. Although we believe this to be unlikely, it will be necessary to determine this to ensure that contamination has not occurred and to control for any dose effect. This will be ascertained using a simple question within the follow-up measure. The reason for not choosing to screen for this at the time of baseline data collection is that doing this may inadvertently draw attention to existence of the ‘games’ and result in participants viewing them out of curiosity resulting in contamination. Data from individuals who viewed the resources prior to delivery of the lesson (intervention group) or before/during study period (control group) will be removed from the analysis.

All questionnaire items will be piloted with approximately five young people prior to use to assess ease of comprehension and the suitability of language. Changes will be made accordingly.

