### Outcomes

#### Primary outcome

Intention to use condoms during vaginal sex with casual sexual partners over the next two months.

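### The ANCOVA covariate list leaves out baseline intention, which the trial collects, and does not say that the risk and coping appraisals enter at baseline

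*Protocol article*

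**What the plan says.** Under the heading on examining the effect of the intervention, the protocol article plans ANCOVA for "differences in condom use intentions (at time two and at follow-up), and behaviour". It then names the covariates: "This will control for demographic variables (gender, ethnicity, age), behaviour at time one, and measures of risk appraisal, and coping appraisal". Behaviour is the only item with a time point attached, and intention is not named.

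Four other places bear on this list:

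- **Primary outcome:** "Intention to use condoms during vaginal sex with casual sexual partners over the next two months".
- **Participant recruitment and baseline assessment:** the baseline questionnaire covers demographics, perceived likelihood, perceived severity, response efficacy and self-efficacy, and also "past behaviour, and intention to use condoms during vaginal sex with casual sexual partners for whom STI status is unknown".
- **Measures post delivery and at follow-up:** of the measures taken straight after the lesson, the article says "These will be a repeat of those taken at baseline". Each appraisal therefore exists in a baseline and a post-lesson version.
- **Methods/design:** "We hypothesise any effects of the intervention on condom use intentions or behaviour will be mediated by risk appraisals and/or coping appraisals". The same appraisals are also secondary outcomes. They are the subject of a mediation analysis, run only if the lesson is found to raise intentions, that is meant to "identify whether changes in risk appraisals and/or coping appraisals are responsible for this change".

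**The concern.** There are two separate questions about one sentence.

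**Omitted baseline value.** The baseline value of the same measure is normally the strongest single predictor of a continuous outcome. Leaving it out of a stated list wastes information already in hand. With about ten units randomised, the arms can easily differ in starting intention by chance, and the listed model would correct that only as far as the other covariates happen to carry it.

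**Undated appraisals.** If the analyst enters the post-lesson appraisals, the model conditions on variables the lesson is designed to change. The group coefficient then no longer answers the primary research question, whether the lesson raises intentions. It estimates roughly the part of the effect that bypasses the appraisals. The mediation analysis depends on a positive effect result, so the better the theory held, the less likely that analysis would be triggered.

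**Working it through.** **Inputs from the protocol article (sample size calculation).** Effect 0.3 (taken as SD units), α = 0.05, power 95%, 484 pupils before inflation, ICC 0.01, ten schools averaging 60 pupils, adjusted total 770.

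**Inputs assumed.** The article gives no correlation between baseline and later intention, and no mediation paths. I take r = 0.4 to 0.7 and state each path used.

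**Step 1: the plan's own figures.** A two-sample t-test at d = 0.3 and 95% power needs 242 per arm, 484 in total, if one-sided. A two-sided test needs 580. The design effect is 1 + 59 × 0.01 = 1.59, and 484 × 1.59 = 769.6, so 770. The figures reproduce and are not in dispute here. The power figures below are two-sided.

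**Step 2: precision from baseline intention.** Adjusting for a covariate with correlation r multiplies residual variance by 1 − r².

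- r = 0.4: 1 − 0.16 = 0.84, a 16% reduction.
- r = 0.7: 1 − 0.49 = 0.51, a 49% reduction.

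The standard error of the arm difference is √(4 × 1.59 × (1 − r²) / N). Degrees of freedom are the number of schools minus 2.

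| Setting | r | SE | 0.3 / SE | Power |
|---|---|---|---|---|
| 10 schools × 60 = 600, 8 df (critical t 2.306) | none | 0.103 | 2.91 | 72% |
| | 0.4 | 0.094 | 3.18 | 79% |
| | 0.7 | 0.073 | 4.08 | 94% |
| 770 pupils, 770/60 ≈ 13 schools, 11 df (critical t 2.201) | none | 0.091 | 3.30 | 85% |
| | 0.4 | 0.083 | 3.60 | 91% |
| | 0.7 | 0.065 | 4.62 | 99% |

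These gains are upper bounds. They apply the same reduction within and between schools, and they start from no covariates at all. Where gender, age, past behaviour or baseline appraisals already explain part of the outcome, baseline intention adds less.

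**Step 3: chance imbalance.** If baseline intention has the same ICC of 0.01, its chance difference between arms with ten schools of 60 has a standard error of √(4 × 1.59 / 600) = 0.103 SD. An imbalance of that size, left unadjusted, moves the outcome difference by r × 0.103, which is 0.04 SD at r = 0.4 and 0.07 SD at r = 0.7, against a design effect size of 0.3.

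**Step 4: what happens if post-lesson appraisals are entered.** Let the lesson shift the appraisal by a SD, let the appraisal-to-intention slope be b, and let the rest be a direct effect. Then total = direct + a × b, and adjusting for the post-lesson appraisal leaves roughly the direct part. Simulation at n = 770 (pupils treated as independent) agrees:

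- a = 0.5, b = 0.4, direct 0.10: total 0.10 + 0.20 = 0.30, adjusted estimate 0.10.
- a = 0.5, b = 0.3, direct 0.15: total 0.15 + 0.15 = 0.30, adjusted estimate 0.15.
- a = 0.6, b = 0.5, direct 0: total 0.30, adjusted estimate about 0.

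As power at 484 effective pupils, if 25%, 50% or 75% of a 0.3 effect is mediated, the remaining 0.225, 0.15 or 0.075 is detected with two-sided power of 70%, 38% or 13%, against 91% for the full effect.

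**Step 5: what happens if baseline appraisals are entered.** In 4,000 simulated trials per scenario, with 484 independent pupils, adjusting for baseline appraisals recovered the total effect of 0.30. Adding baseline intention (entered with coefficient 0.6) still recovered 0.30, and the standard error fell from about 0.08 to about 0.064.

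**The case against.** The strongest reply is that the article means baseline appraisals. The phrase fixing behaviour at time one can be read across the rest of the list. The next paragraph gives changes in appraisal their own mediation analysis, which suggests that the ANCOVA sentence refers to starting levels. The Background also favours a time-ordered design. This reading is plausible, and on it the over-adjustment disappears. A reader might infer from the sentence that the primary estimate will be pulled towards zero. The documents do not support that. They leave both versions open, and the losses in step 4 need both the unfavourable reading and path values that the article does not give. What stands is that the wording permits it.

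It can also be said that omitting a baseline covariate is harmless under randomisation. As to bias in the estimator, that is right. The cost is in precision and in chance imbalance. For the behaviour outcome, the corresponding baseline value is already listed.

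Two further inferences are tempting and should not be drawn:

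- **Loss of inexperienced pupils.** The article expects many pupils without sexual experience ("Given that a large proportion of the sample are not likely to be sexually experienced"), so one might conclude that a covariate for past behaviour would drop them. The coding of that item is in an additional file that is not shown, and it may already have a category for them.
- **Outcome of the mediation model.** One might read the Background as requiring follow-up intention there. It recommends measuring risk appraisal before behaviour and controlling for earlier behaviour. It does not prescribe which intention measure to use.

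Nor is this simply detail left to a fuller document. The article gives a specific list, and it is the content of that list that needs correcting.

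**Conclusion.** The point holds in two parts of different strength.

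The omission of baseline intention is certain on any reading. It is a loss of efficiency and of protection against chance imbalance, not a bias. Its size depends on a correlation that the article does not give. Over r = 0.4 to 0.7 the reduction in residual variance is at most 16% to 49%, with power rising at most from about 72% to 79-94% (ten schools of 60) or from about 85% to 91-99% (770 pupils in about 13 schools).

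The timing of the appraisals is an ambiguity. If post-lesson values were used, a total effect of 0.30 could be reported as 0.10, 0.15 or about zero under the assumed paths. If baseline values are meant, there is nothing to correct beyond the wording. A prespecified primary model should not leave that choice to the analyst.

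**What to change.** Amend the covariate sentence in three respects:

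1. Add baseline intention to the models for intention, both post-delivery and at follow-up.
2. State that risk appraisal and coping appraisal enter the effect models as baseline values only.
3. State that post-lesson appraisals are used only in the mediation analysis and as secondary outcomes in their own right.

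The cost is a sentence or two of text, settled before the analyst sees outcome data by arm. Every variable is already in the baseline questionnaire, so there is no added burden on pupils or schools.

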In addition to strategies to increase chlamydia risk appraisals, the chlamydia lesson incorporates strategies to raise condom use response efficacy (the perceived effectiveness of condoms in reducing the threat of chlamydia) and self-efficacy (beliefs about one’s own ability to use condoms). Protection Motivation Theory (PMT) [12] was developed based on the observation that increasing risk appraisals amongst individuals who do not believe that they are able to perform behaviour can be ineffective. PMT predicts that as individuals’ feelings of threat increase, that protective behaviour will also increase if they feel able to cope with that threat. If on the other hand they feel they can do nothing or little to change their behaviour, then increased perceptions of risk can be counter-productive leading to avoidance (e.g. avoid thinking about STIs), information derogation (e.g. ‘health related messages are over-hyped’), or threat minimisation (e.g. denying you’re at risk of STIs). Evidence concerning whether threat appraisal and coping appraisal (the combined effect of response and self-efficacy) interact or operate in parallel is inconclusive [15]. Until the nature of this relationship has been substantiated, interventions should seek to raise both threat and coping appraisals.

The proposed study uses a two-arm cluster randomised controlled trial (RCT) with a waiting-list control to test the efficacy of an intervention in increasing young adults’ condom use intention and behaviour through changing their chlamydia risk and coping appraisals. This will provide useful information about the ability of persuasive communication to bring about the desired programme effects. The waiting list control design has been chosen to allow all participants to benefit from the lesson. Cluster randomisation has been chosen to prevent within-school contamination.

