#### Secondary research questions

•Is the lesson effective in increasing young people’s *condom use* during vaginal sex with casual sexual partners?

•If the lesson is effective, are changes in young people’s condom use intentions or behaviour due to changes in their chlamydia risk appraisals (perceived likelihood and severity) and/or coping appraisals (condom use response efficacy and self-efficacy)?

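### Planned mediation analysis covers intention only, and only if intention rises, although the mechanism question and hypothesis cover intentions or behaviour

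*Protocol article*

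**What the plan says.** In the Protocol article, under *To examine the effect of the intervention*, an ANCOVA of intention (time two and follow-up) and of behaviour is planned without condition. Mediation is planned with one: "If the lesson is effective in increasing condom use intentions, mediation analysis" follows. Its purpose is "to identify whether changes in risk appraisals and/or coping appraisals are responsible for this change", and the change referred to is the one in intentions.

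Three other places set a wider aim:

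- *Secondary research questions*: "If the lesson is effective, are changes in young people’s condom use intentions or behaviour due to changes in their chlamydia risk appraisals" and/or coping appraisals.
- *Methods/design*: "We hypothesise any effects of the intervention on condom use intentions or behaviour will be mediated by risk appraisals and/or coping appraisals".
- *Background*: the study will allow "examination of whether an increase in chlamydia risk appraisals is sufficient to increase condom use intentions and/or behaviour", and will show "whether a failure to change behaviour is the result of a failure to increase condom use intentions" or of stronger factors acting when intention is turned into behaviour.

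The four appraisals (perceived likelihood, perceived severity, response efficacy, self-efficacy) are listed under *Secondary outcomes*. Under *Measures post delivery and at follow-up* they are measured again right after the lesson, and condom use is measured at follow-up.

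**The concern.** The plan states a rule for mediation that is narrower than the question it is meant to answer, in two ways.

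1. **Outcome.** The question and the hypothesis name two outcomes; the analysis names one. A change in condom use would have no planned explanation, whether or not intention also changed.
2. **Condition.** Whether raised risk appraisal is sufficient matters most when intention does not rise. An answer then needs the lesson's effect on the appraisals (path a) and the relation of appraisal to outcome (path b). The stated rule stops before either is estimated.

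At stake is a secondary, explanatory aim. The Discussion intends to draw conclusions about the place of risk appraisal in theories of health behaviour. A null on intention would mean one thing if the lesson failed to move appraisals and another if it moved them without effect.

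**Working it through.** **Step 1. What the stated analyses answer in each pattern of results.**

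| Intention | Condom use | What the plan delivers | What is left open |
|---|---|---|---|
| rises | rises | ANCOVAs; mediation of intention | mediation of condom use |
| rises | no change | ANCOVAs locate the break after intention; mediation of intention | nothing that the Background promises on this pattern |
| no change | rises | ANCOVAs only | mediation of condom use |
| no change | no change | ANCOVAs show that both are null | whether appraisals moved, and if so whether they were insufficient |

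Three of the four patterns leave part of the stated aim without an analysis. The data do not force this, because mediators are measured after delivery and condom use at follow-up. The ANCOVA lists appraisal measures as covariates without giving their time point, and its outcomes are intention and behaviour. It is therefore not a stated estimate of the lesson's effect on the appraisals.

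**Step 2. The plan's own sample size, which governs how often the condition is met.** Inputs from *Sample size calculation*: effect 0.3, α = 0.05, power 95%, ICC 0.01, cluster size 60.

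- A two-sample t-test gives 241.2, so 242 per arm, total 484, if one-sided. Two-sided it gives 289.7, so 290 per arm, total 580. The stated 484 reproduces as one-sided.
- Design effect 1 + 59 × 0.01 = 1.59, and 484 × 1.59 = 769.6, the stated 770.

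**Step 3. Chance that the condition is met.** The protocol gives no criterion for *effective*, so two-sided p < 0.05 is assumed. Effective n per arm is 770 / 1.59 / 2 = 242.1. Power = Φ(d × √(242.1/2) − 1.96):

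- d = 0.3: Φ(3.30 − 1.96) = 0.91
- d = 0.2: Φ(2.20 − 1.96) = 0.60
- d = 0.15: Φ(1.65 − 1.96) = 0.38

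This takes no account of the small number of schools. With 10 schools of 60, five per arm, a t-test on school means has 8 df. The variance of a school mean is 0.01 + 0.99/60 = 0.0265 and the SE of the difference is √(2 × 0.0265/5) = 0.103. At 0.3 the non-centrality is 0.3/0.103 = 2.91 and power is about 0.72.

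**Step 4. Would an unconditional test of the indirect effect do better?** It depends on path a, which the protocol does not give. Simulated power (10 × 60, two-sided 5%; joint test of path a on school means and path b within schools):

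| Assumed paths | ICC | Total-effect test | Joint test of a and b |
|---|---|---|---|
| a = 0.6, b = 0.5, full mediation, total 0.3 | 0.01 | 72% | over 99% |
| same | 0.03 | 48% | 97% |
| a = 0.3, b = 0.5, partial mediation, total 0.3 | 0.01 | 74% | 72% |
| same | 0.03 | 48% | 49% |
| a = 0.3, b = 0.5, full mediation, total 0.15 | 0.01 | 26% | 74% |

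Path b is estimated within schools from many pupils and is almost always significant, so the joint test is about as powerful as the test of path a. Path a faces the same between-school comparison and 8 df as the total effect. At a = 0.3 and total 0.3 the two non-centralities are both 2.91, so the advantage vanishes.

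**The case against.** **Conditioning matches the question.** The secondary research question itself begins with the lesson being effective, and testing mediation only after a total effect is a recognised if dated approach. This stands in part. It does not justify tying the condition to intention alone, since the question names behaviour as well, and it does not meet the Background's aim of examining sufficiency. The protocol also says effective, not significant; the significance criterion above is an assumption.

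**The detail may be in the SAP.** Much about mediation can be left there. The point here is that the protocol states the rule, and states it more narrowly than its own question.

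**Behaviour has little weight.** The Background expects a large sexually inexperienced share and says intention is therefore needed as the outcome for the motivational hypothesis. This stands as a reason to call mediation of condom use exploratory, but not to omit it after hypothesising it.

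Three stronger readings are tempting and not supported:

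- *The motivational hypothesis goes wholly untested.* It does not. The ANCOVAs run unconditionally and show whether a null on behaviour goes with a null on intention, and the intention mediation still runs if intention rises and behaviour does not.
- *The plan expects opposing pathways that cancel.* The Background says that "increased perceptions of risk can be counter-productive leading to avoidance", but among people who feel unable to cope, and the lesson targets coping for that reason. That is moderation, not a uniform negative direct effect. Simulated as such (a = 0.5, b = +0.3 in half the pupils and −0.3 in the other half, ICC 0.01), the total effect is significant in 5% of trials and the joint test in 7%, so simple unconditional mediation would miss it too.
- *An unconditional test is generally much better powered.* With a total effect at the planned 0.3, that needs a path a of about 0.6. The protocol's only anchor is 0.3, from a meta-analysis covering risk appraisals, intentions and behaviour, and at that value the two tests are about equal.

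**Conclusion.** The point holds as a contradiction within the protocol. Mediation is limited to intention and depends on an intention effect, while the secondary question and the hypothesis cover intentions or behaviour and the Background promises to examine sufficiency for either. Two things lack a stated analysis: mediation of any effect on condom use, and, when intention does not rise, the distinction between appraisals that did not change and appraisals that changed but were insufficient.

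This conclusion rests on the text and needs no numerical assumption. The probabilities of meeting the condition are illustrations under a significance criterion and path sizes that the protocol does not give. The primary result and the sample size are unaffected.

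**What to change.** Replace the conditional sentence under *To examine the effect of the intervention* with a plan that, whatever the intention result:

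- estimates the lesson's effect on each of the four appraisals, already listed as secondary outcomes;
- estimates the indirect effects through them, with confidence intervals that allow for clustering by school;
- does so for intention and, labelled exploratory because few pupils will contribute, for condom use at follow-up among sexually experienced pupils;
- reads a null on intention through the two paths, so that no change in appraisal is told apart from a change that was not enough.

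The cost is a wording change and a few more secondary estimates to report. No new data are needed.
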